##### Primary Analyses

The primary outcomes are adherence (percent of sessions attended, percent of home exercises completed). The primary analysis method is repeated measure analysis of variance (ANOVA) between the two groups or the non parametric equivalent (Friedman procedure). We will subtract baseline value from the 2- and 4-month assessment values and use residualized change scores from baseline as the outcome. We will use the Tukey-Fisher criteria for post hoc mean/median comparisons under the ANOVA or Friedman model. The same methods will be used for the analyses on NRS and FDI scores.

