**Methods:**

This protocol will recruit adolescents ages 12-17 with chronic pain and randomly assign them to either peer mentorship or a treatment-as-usual control group. Mentored participants will be matched with peer mentors of similar age (ages 14-18) who have actively participated in various treatment modalities through the UCLA Pediatric Pain Program and have learned to function successfully with a chronic pain disorder. The mentors will present information to mentored participants in a supervised and monitored telephone interaction for 2 months to encourage participation in skill-building programs. The control group will receive usual care but without the mentorship intervention. Mentored and control subjects' pain and functioning will be assessed at 2 months (end of intervention for mentored participants) and at 4 month follow-up to see if improvements persist. Measures of treatment adherence, pain, disability, and anxiety and depression will be assessed throughout study participation. Qualitative interviews for mentors, mentored participants, and control subjects will also be administered.

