### Aims

1. To test the feasibility and acceptability of a peer-mentorship intervention in supporting and encouraging adolescents with chronic pain and pain-related functional disability (the "mentored participants") to participate and persist in an active skills-building therapy that teaches pain self-management skills.

2. To test the feasibility of training adolescents who have coped successfully with chronic pain (the "mentors") to offer support and reinforcement to their peers in a structured peer-mentorship intervention, based on a manualized protocol developed within a social learning model grounded in CBT principles.

3. To determine if the mentored participants with chronic pain show improved adherence to recommended skills-building therapies, compared to a usual care control group of adolescents with chronic pain immediately after the two-month peer-mentorship intervention and at two-month follow-up (four months from baseline).

4. To determine if the mentored participants with chronic pain show improvements in pain levels and pain-related disability, compared to a usual care control group of adolescents with chronic pain immediately after the two-month peer-mentorship intervention and at two-month follow-up.

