### Randomization

Participants recruited for the mentored or control portion of the study will be randomized using a block randomization procedure to assure equal sample sizes in the mentoring and control groups. Using this method allows the groups to have similar numbers of participants in each group at all times. Using a block size of 4, participants are assigned to the appropriate treatment condition as they enroll in the study until the block is completed. Then the following 4 participants are assigned based on the next block [36].

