##### Preliminary Analyses

Once the data set has been cleaned and examined for skewness and missing data, exploratory data analyses will be conducted using univariate methods to describe the variables of interest and bivariate techniques to characterize their interrelationships within our sample. Continuous variables will be summarized over time in each group using means and medians and we will also report their range, interquartile range and standard deviations. Cross tabulated frequencies will be given for all discrete variables by group and time. Both parametric and non parametric correlations will be reported. Results from these descriptive analyses will be used to help guide the primary analyses by providing information about potential problem measures (e.g., heavily skewed distributions) or problematic variable relationships (e.g., highly correlated predictors) and will help determine if transformations of some outcomes (such as percent adherence) are possible in order to use parametric methods. Only after a full descriptive investigation of the dataset has been achieved and potential problem variables identified will primary analyses commence. Potential covariates will be examined prior to final statistical modeling to determine whether there are pre-existing differences between the groups. These exploratory analyses will test for differences in demographic and clinical parameters as well as psychological aspects that have been found to correlate with functioning in our prior work. We will also look at mentored participant outcomes within and across mentors to attempt to determine if there are any discernable patterns of improvement or decline in functioning as a function of clustering of outcomes within mentors or outcomes as a function of each mentor's experience with the protocol. This will help account for therapist effects as well as potential learning and/or fatigue effects. Any variables found to vary significantly by group will be included as covariates in primary and secondary analyses. This will also serve to verify that the randomization was successful.

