##### Secondary Analyses

Repeated measure analysis of variance (ANOVA) between the two groups or the non parametric equivalent (Friedman procedure) will also be used to evaluate differences in anxiety and depressive symptoms (RCADS, CASI) and additional measures. We will also look at the relation between session attendance (percent sessions attended) and home exercise completion (percent exercises completed) versus FDI change from baseline. The relation will be quantified by the Pearson and Spearman correlations. If appropriate, we will also use regression methods and report intercepts and slopes.

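### The nonparametric fallback named for the two-group analyses, the Friedman procedure, has no between-group term and cannot test mentoring if it is used

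*Protocol article*

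**What the plan says.** Under Primary Analyses the protocol article gives one method and one alternative: "The primary analysis method is repeated measure analysis of variance (ANOVA) between the two groups or the non parametric equivalent (Friedman procedure". It defines the scores to be analysed: "We will subtract baseline value from the 2- and 4-month assessment values and use residualized change scores from baseline as the outcome". It adds a post hoc step: "We will use the Tukey-Fisher criteria for post hoc mean/median comparisons under the ANOVA or Friedman model". The section extends all of this to NRS and FDI. Secondary Analyses repeats the pairing: "between the two groups or the non parametric equivalent (Friedman procedure) will also be used to evaluate differences in anxiety and depressive symptoms".

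Preliminary Analyses shows when the alternative might come into play. The descriptive work "will help determine if transformations of some outcomes (such as percent adherence) are possible in order to use parametric methods".

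The comparison is between independent arms. The abstract says the trial will "randomly assign them to either peer mentorship or a treatment-as-usual control group", and Aim 3 asks whether mentored participants "show improved adherence to recommended skills-building therapies, compared to a usual care control group". No rank test that compares two independent groups is named anywhere in the article.

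**The concern.** Friedman is the rank counterpart of a one-sample, within-subject ANOVA. It asks whether the repeated occasions differ from one another. It has no between-subject factor and no group-by-time term, so it does not replace a repeated-measures ANOVA that compares two arms.

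The article therefore names the wrong test; this is more than a detail left for a later plan to fill in. An analyst who finds percent adherence too skewed to transform, and follows the text, would have no test of the primary question. An analyst who notices the problem would have to choose a replacement test at that stage, possibly with the data already in view.

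**Working it through.** **Inputs.** Two independent arms (abstract; Randomization). Two scores per subject, at 2 and 4 months (Primary Analyses). From Sample Size Determination and Power Analysis: 29 per group, effect size 0.52, two-sided alpha 0.05. Assumed here because the article gives no value: within-subject correlation 0.5, normal data, SD 1. The article states no figure for this fallback, so there is none to reproduce; 29 and 0.52 only set the scale.

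**Step 1: the statistic.** With two repeated scores, let s be the number of the N subjects whose 4-month score exceeds their 2-month score. Friedman reduces to a sign test:

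Q = (2s − N)² / N, on 1 df.

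The arm label does not appear. With N = 58, s = 36 gives 14²/58 = 3.38 and s = 37 gives 16²/58 = 4.41. The test therefore rejects at s ≥ 37 or s ≤ 21.

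**Step 2: effect of mentoring on the statistic.** A lasting mentoring effect adds the same constant to both scores of a mentored subject. The sign of the within-subject difference does not change, so s and Q do not change. The same holds after residualizing on baseline with a pooled regression at each visit, because the constant shifts both residuals equally and cancels in their difference.

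Numerical check on 58 simulated subjects:
- Three visits: Q = 4.379. It stays 4.379 after reordering subjects across arms and after adding 100 to every mentored value.
- Two change scores: Q = 0.069 (= 2²/58) before and after adding 100 to every mentored change.

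This step needs no assumption about correlation or distribution.

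**Step 3: rejection rates.** Simulation, 29 per arm, correlation 0.5. The rank-sum test is applied to each subject's mean over the two visits.

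| Scenario | Friedman, simple change | Rank-sum, simple change | Friedman, residualized | Rank-sum, residualized |
|---|---|---|---|---|
| Mentoring effect 0.52 SD | about 5% | about 58% | about 0.1% | about 75% |
| Mentoring effect 1.5 SD | about 5% | 100% | about 0.1% | 100% |
| No mentoring effect, shared 0.5 SD shift from month 2 to month 4 | about 84% | about 5% | near 0% | about 5% |

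Residualized scores average zero at each visit over the pooled sample. This holds s near N/2 and explains why Friedman almost never rejects there.

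The last row can be checked by hand for simple change scores. The chance that a subject's later score exceeds the earlier one is Φ(0.5/√(2(1 − 0.5))) = Φ(0.5) = 0.691. The chance that s reaches 37 or more of 58 is then about 85%, in line with the simulation.

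**Step 4: other ways to apply Friedman.**
- Arms as columns and visits as blocks, one summary value per cell: with two columns the largest possible Q equals the number of blocks. Two visits give p = 0.157 at best (exact 0.50), and three give p = 0.083 (exact 0.25). Significance at 0.05 cannot be reached.
- Separately within each arm: this gives no comparison between arms.
- Randomization blocks as Friedman blocks: the article describes them only as an allocation device ("Using a block size of 4, participants are assigned to the appropriate treatment condition as they enroll in the study") and never as analysis strata.

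**The case against.** The best defence is that the fault is narrow. The first-named method, repeated-measures ANOVA between the groups, does test mentoring. The article's wording shows that a between-group comparison is intended throughout, so this is a misnamed test and not a decision to test time. The trial is an exploratory pilot whose first two aims concern feasibility. All of that stands, and it limits the reach of the point. It does not repair the fallback: no valid rank test is named, and the post hoc step is tied to the ANOVA or Friedman model and supplies no separate group test.

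Three stronger readings are tempting, and the document does not support them.
- *The primary analysis as a whole fails to test mentoring.* Only the conditional alternative fails.
- *The fallback is likely to be used.* Preliminary Analyses prefers transformation so that parametric methods can be kept, and names percent adherence as a candidate for it. Use of Friedman is possible, but nothing says it is expected.
- *The fallback would produce false positives whenever both arms drift.* The 84% figure applies only to simple change scores. Primary Analyses speaks both of subtracting baseline and of residualized change. On residualized scores a shared shift is removed before the test is run.

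A further reply is that Friedman on three raw visits does react to mentoring: in simulation it rejects 35% of the time at 0.52 SD with control flat. But it rejects 94% of the time when both arms improve by 0.52 SD and mentoring does nothing, so it cannot separate the two. Raw visits are also not the scores the section specifies.

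**Conclusion.** The point holds for the fallback branch. As written, that branch cannot detect a lasting mentoring effect on adherence, NRS, FDI or the secondary outcomes, however large the effect. This follows from the form of the statistic alone. The percentages rest on 29 per arm, an assumed correlation of 0.5 and normal data, and would move with those assumptions. The main harm is a lost test; false signals from shared drift are an added harm only if simple change scores are used. That the rank-sum test reaches about 58% or 75% at 0.52 SD, short of the planned 80%, is a separate sample-size matter and not part of this point.

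**What to change.** In Primary Analyses and Secondary Analyses, replace the Friedman procedure with one between-group rank method. A suitable choice is a Wilcoxon rank-sum test of mentored against control subjects on each subject's mean residualized change over months 2 and 4. Separate rank-sum comparisons at 2 and at 4 months can be listed as supportive, so that they do not become two uncoordinated primary tests. State whether the score is simple or residualized change, and remove the reference to a Friedman model from the post hoc sentence. Fix the choice, and the condition that triggers it, before outcomes are viewed by arm. The cost is wording only: no change to design, data collection or sample size.

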##### Secondary Analyses

Repeated measure analysis of variance (ANOVA) between the two groups or the non parametric equivalent (Friedman procedure) will also be used to evaluate differences in anxiety and depressive symptoms (RCADS, CASI) and additional measures. We will also look at the relation between session attendance (percent sessions attended) and home exercise completion (percent exercises completed) versus FDI change from baseline. The relation will be quantified by the Pearson and Spearman correlations. If appropriate, we will also use regression methods and report intercepts and slopes.

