### Hypotheses

We propose to test our hypotheses through a trial of a peer mentorship intervention, using trained adolescents who have successfully learned pain management skills as mentors. The mentors will help to relieve the adolescents' sense of isolation and difference by relating their similar experiences, provide models of successful skill learning and reinforce the mentored participants' participation in skill learning activities. We propose the following hypotheses:

1. Adolescents receiving the peer mentorship intervention will report better adherence to recommended therapies, as compared to adolescents who do not receive the intervention.

2. Adolescents with better adherence to recommended therapies will show more improvement in pain and pain-related disability 2 and 4 months after baseline than those with poor adherence.

3. Adolescents receiving the peer mentorship intervention will report decreased symptoms of anxiety and depression and improved pain coping skills, as compared to adolescents who do not receive the intervention.

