### Statistical analysis

#### Sample size

##### Sample Size Determination and Power Analysis

The proposed sample size was calculated with two objectives in mind: 1) to remain realistic in terms of recruitment based on our anticipated patient flow and the proposed time frame; and 2) to ensure the power to detect significant group differences in the primary outcome measures. Based on our average patient intake of 8-12 new patients a month and the parameters of our existing population, we estimate that we will be able to recruit 3-4 per month in the target age group (12-17) to participate in this pilot study, or a minimum *N *of 50. About 70% will be girls, 30% boys. The majority will be non-Hispanic white, but about 33% will be from other ethnic groups or of mixed-race. The second objective in calculating the proposed sample size is to ensure adequate power (.80) to detect variable relationships (two-tailed, *p *< .05) when conducting the primary analyses. Since there have been no comparable studies of peer mentorship interventions and there are no data available to calculate effect sizes for adherence to skill-based therapies in a pediatric chronic pain population, we have chosen the conservative strategy of extrapolating from other studies of pediatric pain that have used the Functional Disability Inventory (FDI) [39] as an outcome measure in evaluating a CBT-based intervention, in making our power calculations. One study [45] included 30 adolescents with fibromyalgia randomized to either 8 weeks of coping skills training or control (self-monitoring) and then crossed-over to the alternate condition. For the FDI, the authors reported overall effect sizes of 1.29 for patients (n = 14) who received the self-monitoring first and then the coping skills training and 0.52 for patients (n = 13) who received the coping skills training followed by self-monitoring. A second study examined an 8 week CBT trial in 44 adolescents with fibromyalgia [46]. These authors found a significant reduction in the FDI following treatment compared to waitlist control, with an effect size of 0.75. Using the smallest effect size reported in these two studies (i.e., .52), which corresponds to a medium sized effect according to the conventions proposed by Cohen [47], with power of .80 to detect a significant difference in FDI scores using two-tailed tests and with alpha set at .05, it is estimated that we will be able to detect this effect size with 29 subjects per group.

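### The only planned analysis of Hypothesis 2 is a simple correlation with no treatment-arm term, no stated change score and no pain outcome, so an arm difference can pass for an adherence benefit

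*Protocol article*

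**What the plan says.** All references are to the protocol article.

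- **Hypotheses, item 2:** "Adolescents with better adherence to recommended therapies will show more improvement in pain and pain-related disability 2 and 4 months after baseline" than poor adherers. Two outcomes and two time points are named, and the comparison is between adolescents by adherence, not by arm.
- **Secondary Analyses:** percent of sessions attended and percent of home exercises completed are set "versus FDI change from baseline. The relation will be quantified by the Pearson and Spearman correlations". Then: "If appropriate, we will also use regression methods and report intercepts and slopes". No covariate and no time point is named, and NRS does not appear in this comparison.
- **Primary Analyses:** "We will subtract baseline value from the 2- and 4-month assessment values and use residualized change scores from baseline as the outcome". This sentence names both a simple difference and a residualized change. The section extends its methods to NRS and FDI, but for the comparison between groups.
- **Preliminary Analyses:** "Any variables found to vary significantly by group will be included as covariates in primary and secondary analyses".
- **Hypotheses, item 1:** "Adolescents receiving the peer mentorship intervention will report better adherence to recommended therapies, as compared to adolescents who do not receive the intervention". The text introducing the hypotheses adds that mentors will "relieve the adolescents' sense of isolation and difference by relating their similar experiences", and item 3 expects better pain coping.

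**The concern.** Hypothesis 2 is one of three stated hypotheses, and its analysis falls short of it in three ways.

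1. **Arm.** If mentoring raises adherence and also lowers FDI by a route other than therapy attendance, mentored adolescents will on average have both higher adherence and more improvement. A correlation over all participants then contains that arm difference even if attendance does nothing. The covariate rule in Preliminary Analyses does not help: it admits characteristics that differ between the groups, and arm is the grouping itself.
2. **Change score.** Raw change and residualized change answer different questions when the exposure is not randomised, and Secondary Analyses does not say which is meant.
3. **Pain.** Half of the hypothesis has no stated analysis.

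At stake is how the pilot's adherence result is read. The Discussion plans a larger trial with a mediator/moderator model, and a misleading association between adherence and outcome could carry into its design.

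**Working it through.** **Figures in the plan.** The article gives no power or error figure for the Hypothesis 2 correlation. Its only power statement concerns the comparison of FDI between groups, "with power of .80 to detect a significant difference in FDI scores using two-tailed tests and with alpha set at .05", with effect size 0.52 and 29 per group. A standard two-sample calculation gives 59 per group for those inputs, so 29 is not reproduced. That is a separate matter; 29 per arm is used here only as a sample size.

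**Inputs**

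- From the article: equal allocation, two-sided alpha 0.05 (so 2.5% in the direction of benefit), 29 per arm. The FDI effect sizes 0.52 and 0.75 are those it cites from other trials.
- Assumed, because the article gives none: FDI baseline-to-follow-up correlation ρ = 0.5 (range 0.3 to 0.7); arm effect on adherence dA = 0.5 or 0.8 SD; arm effect on FDI by routes other than adherence dF = 0.52 or 0.75 SD.
- Adherence has no effect on FDI. Improvement is baseline minus follow-up FDI, so a positive correlation looks like benefit.

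**Step 1: correlation produced by combining arms.** With two equal arms, the covariance between adherence and improvement due to arm is dA·dF/4. Hence

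r = (dA·dF/4) / √[(1 + dA²/4)·(2(1−ρ) + dF²/4)]

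- dA = 0.5, dF = 0.52: 0.065 / √(1.0625 × 1.0676) = 0.065/1.065 = 0.06.
- dA = 0.8, dF = 0.75: 0.150 / √(1.16 × 1.1406) = 0.150/1.150 = 0.13.
- If either dA or dF is zero, r = 0.

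**Step 2: false benefit rate.** Simulation, 20,000 trials per setting, ρ = 0.5, Pearson correlation over both arms:

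| dA, dF | n per arm | mean r | false benefit (nominal 2.5%) |
|---|---|---|---|
| 0.5, 0 | 29 | 0.00 | 2.8% |
| 0, 0.52 | 29 | 0.00 | 2.6% |
| 0.5, 0.52 | 29 | 0.06 | 6.7% |
| 0.8, 0.75 | 29 | 0.13 | 16.6% |
| 0.5, 0.52 | 48 | 0.06 | 8.7% |
| 0.8, 0.75 | 48 | 0.13 | 25.0% |

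A second run with a different seed gave 6.4% and 16.5% for the third and fourth rows, and Spearman gave 6.4% and 16.1%. For dA = 0.5 and dF = 0.52, the rate was 5.5% at ρ = 0.3 and 8.2% at ρ = 0.7.

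**Step 3: what an arm term does.** With arm in the model, mean r was 0.00 and false benefit about 2.5% in these settings, whether the outcome was raw change or follow-up FDI given baseline. Residualizing the change without an arm term does not remove the problem: r was 0.07 and 0.15 in the two main settings.

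**Step 4: why the change score has to be stated.** Let c be the correlation of adherence with baseline FDI, with no adherence effect and no arm effects, 29 per arm, ρ = 0.5.

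- *Adherence depends on the observed baseline score.* Raw change has induced r = c·√((1−ρ)/2). At c = 0.3 this is 0.3 × 0.5 = 0.15, with false benefit 20.5%. At c = −0.3 it is −0.15, with false harm 19.9% and false benefit 0.1%. Baseline adjustment gives r = 0.00.
- *Adherence depends on a stable underlying level of disability that both scores measure with error.* Raw change is unbiased (r = 0.00). Baseline adjustment gives a partial correlation of size |c|·(1−ρ)/√[(1−c²)(1−ρ²)] = 0.15/√(0.91 × 0.75) = 0.18. At c = −0.3 it is in the direction of benefit, with a false benefit rate of about 26%.

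Each analysis is therefore sound under one model and biased under the other.

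**The case against.** The strongest case on the other side has five parts.

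- **Pooling is not stated.** True. Secondary Analyses does not say that the arms are combined. Combining them is the natural reading of a hypothesis that compares adolescents by adherence, but it is a reading.
- **Residualized change may be meant.** It may, since Primary Analyses names it just before. That would remove the baseline part under the first model in Step 4, but it leaves the arm part and the missing pain analysis.
- **Covariates are ordinarily left to the analysis plan.** This is fair for the optional regression. The correlations, however, are the analysis that the article does fix, and the one covariate rule it states cannot bring in arm.
- **The stakes are modest.** This stands. It is a secondary analysis in an exploratory pilot, the section attaches no decision rule to it, and Hypothesis 2 is itself worded as an association.
- **The arm effect needs two conditions.** This also stands. Mentoring must change both adherence and FDI by other routes; either alone gives no bias.

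A reader might infer something stronger: that correlating adherence with change builds in regression to the mean, so the plan favours a false adherence benefit and baseline adjustment is the correct test. The article does not support this. It does not say that the change is raw and gives no figure for how adherence relates to baseline FDI. If more disabled adolescents attend less, the bias in raw change runs towards false harm. If adherence follows stable disability, baseline adjustment is itself the biased analysis.

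**Conclusion.** The concern holds in a limited form. The analysis of Hypothesis 2 names no arm term, does not define its change score and omits pain; these gaps are visible in the text. The arm problem has a size only under assumptions that the article does not supply: r of about 0.06 to 0.13 and false benefit of about 6.5% to 16.5%, against 2.5%, at 29 per arm. It rests on the arms being combined and on mentoring affecting both adherence and FDI by other routes. The article makes both routes plausible but quantifies neither. No direction of bias from baseline disability can be claimed. An arm term would not make the adherence result causal, because adherence is not randomised and other confounding remains. Priority is low to moderate.

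**What to change.** Reword the Hypothesis 2 analysis as follows.

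- Fit a linear regression on percent adherence with randomised arm as a covariate, for FDI and separately for NRS, at 2 and at 4 months. Reporting the correlations within each arm is an acceptable alternative to the arm term.
- State whether change is raw or residualized, and report both the change-score estimate and the baseline-adjusted estimate. If they disagree, say so rather than choosing one.
- Report the adherence slope with a 95% confidence interval and call it an association.
- Keep the Pearson and Spearman correlations as description.

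Cost: wording, somewhat more analysis, and about one degree of freedom for arm. FDI, NRS and treatment tracking are already scheduled at baseline, 2 and 4 months in Table 1. The arm term also gives up the part of the adherence variation that lies between arms, (dA²/4)/(1 + dA²/4): 0.0625/1.0625 = 6% at 0.5 SD and 0.16/1.16 = 14% at 0.8 SD, so the slope is slightly less precise.
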